### **6.4 Withdrawal of individual subjects**

Subjects can leave the study at any time for any reason if they wish to do so without any consequences. The investigator can decide to withdraw a subject from the study for urgent medical reasons. Each withdrawal must be clearly documented.

## **7. SAFETY REPORTING**

Both arms of the study are existing and accepted surgical strategies. The fertility surgeons participating master both techniques equally well.

### **7.1 Temporary halt for reasons of subject safety**

The DSMB can terminate the study if in their opinion a significant number of adverse events have occurred as a result of performing the study. Although unexpected severe adverse events are not anticipated since this trial compares two existing and accepted surgical strategies.

### **7.2 Definitions AEs, SAEs and SUSARs**

#### **7.2.1 Adverse events (AEs)**

An AE is any untoward medical occurrence in a patient or subject during an experiment, and which does not necessarily have a causal relationship with the specific surgical intervention. An AE can therefore be any unfavourable and unintended sign (including an abnormal laboratory finding), symptom or disease temporally associated with the use of a specific intervention, whether or not considered related to the intervention. Any worsening (i.e., any clinically significant adverse change in the frequency or intensity of a pre-existing condition) should be considered an AE.

#### **7.2.2 Serious adverse events (SAEs)**

A serious adverse event is any untoward medical occurrence or effect that

- results in death;
- is life threatening\* (at the time of the event);

- requires hospitalization or prolongation of existing inpatients' hospitalization;
- results in persistent or significant disability or incapacity;
- is a congenital anomaly or birth defect; or
- any other important medical event that did not result in any of the outcomes listed above due to medical or surgical intervention but could have been based upon appropriate judgement by the investigator.

An elective hospital admission will not be considered as a serious adverse event.

*\* The term "life threatening" in the definition of SAE refers to an event in which the subject was at risk of death at the time of the event. It does not refer to an event which hypothetically might have caused death if it was more severe.*

### **7.2.3 Suspected Unexpected Serious Adverse Reaction (SUSAR)**

A SUSAR is an adverse reaction, the nature or severity of which is not consistent with the information on the experiment, and, when a clinical trial is concerned, with the applicable product information (e.g. the patient leaflet joined to the summary of product characteristics for an authorised product).

### **7.3 Adverse events that do not require reporting**

The following events are considered reportable:

- any SAE\*
- reintervention for bleeding on the operated ovary
- POI

\*For this study the following serious adverse events are not to be considered as SAE and should not be reported to the Sponsor, these should be recorded in the patient's medical notes according to routine practice:

- Pre-planned hospitalizations unless the condition for which the hospitalization was planned has worsened from the first trial-related activity after the subject has signed the informed consent.
- Hospitalization as part of a standard procedure for protocol therapy execution. However, hospitalization or prolonged hospitalization for a complication of the intervention will be reported as an SAE.
- Hospitalization or prolongation of hospitalization for technical, practical, or social reasons, in absence of an AE.
- Treatment of a pre-existing disease that is not aggravated
- Treatment of a pre-existing disease that has not worsened

In general, the following should not be reported as AEs:

- Pre-existing conditions, including those found as a result of screening (these should be reported as medical history or concomitant illness).
- Pre-planned procedures unless the condition for which the procedure was planned has worsened from the first trial-related activity after the subject has signed the informed consent.

#### 7.4 Recording and reporting of Adverse events

Investigators will seek information on AEs during each patient contact. All events, whether reported by the patient or noted by trial staff, will be recorded in the patient's medical record and in the (e)CRF within a reasonable time after becoming aware. If available, the diagnosis should be reported on the AE page, rather than the individual signs or symptoms. If no diagnosis is available, the Investigator should record each sign and symptom as individual AEs.

The following minimum information should be recorded for each AE:

- AE description
- start and stop date of the AE
- severity
- seriousness
- causality assessment to the study interventions
- outcome

##### 7.4.1 Assessment

All AEs must be evaluated by an Investigator as to:

- Seriousness: whether the AE is an SAE. See above for the seriousness criteria.
- Severity: Severity must be evaluated by an Investigator according to the following definitions:
  - Mild – no or transient symptoms, no interference with the subject's daily activities
  - Moderate – marked symptoms, moderate interference with the subject's daily activities
  - Severe – considerable interference with the subject's daily activities, unacceptable
- Causality:
  - None – An AE which is not related to the study-related interventions
  - Unlikely – An AE for which an alternative explanation is more likely (e.g. concomitant medication(s), concomitant disease(s)), and/or the relationship in time suggests that a causal relationship is unlikely
  - Possible – An AE which might be due to the study-related interventions. An alternative explanation is inconclusive. The relationship in time is reasonable; therefore the causal relationship cannot be ruled out.
  - Probable - An AE which might be due to the study-related intervention. The relationship in time is suggestive (e.g. confirmed by dechallenge). An alternative explanation is less likely.
  - Definitely – An AE which is known as a possible adverse reaction and cannot be reasonably explained by an alternative explanation. The

relationship in time is very suggestive (e.g. it is confirmed by dechallenge and rechallenge).

#### **7.4.2 Timeline for reporting**

All reportable events will be reported, without undue delay after obtaining knowledge of the events, to the sponsor and chief investigator by mail. This reporting is done by using the appropriate SAE form (in the eCRF). The following information will be recorded: description, date of onset and end date, severity, assessment of relatedness to the specific surgical technique. Follow up information should be provided as necessary.

#### **7.4.3 Follow-up**

The Investigator must record follow-up information by updating the medical records and the appropriate forms in the (e)CRF. The worst-case severity and seriousness of an event must be kept throughout the trial.

SAE follow-up information should only include new (e.g. corrections or additional) information and must be reported within 24 hours of the Investigator's first knowledge of the information.

This is also the case for previously non-serious AEs which subsequently become SAEs.

- All SAEs must be followed up until the outcome of the event is 'recovered', 'recovered with sequelae', 'not recovered' (in case of death due to another cause) or 'death' (due to the SAE) and until all related queries have been resolved, or until end of trial (whichever occurs first).
- Non-serious AEs must be followed up until the patient's last study visit, and until all related queries have been resolved.

SAEs after the end of the trial: If the Investigator becomes aware of an SAE with suspected causal relationship to the study-related interventions after the subject has ended the trial, the Investigator should report this SAE within the same timelines as for SAEs during the trial.

All reportable AEs will be followed until they have abated, or until a stable situation has been reached. Depending on the event, follow up may require additional tests or medical procedures as indicated, and/or referral to the general physician or a medical specialist.

#### 7.4.4 Pregnancy

Female subjects must be instructed to notify the Investigator immediately if they become pregnant during the trial. Pregnancy is a secondary outcome in the study, is no (S)AE and should therefore not be reported to the Sponsor.

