#### Secondary Objectives:

- AMH difference/cyst surface  
between baseline and at 3, 6 and 12 months post-operative with a correction for the cyst surface (since the volume of the cyst may be responsible for more/less influence on the ovarian reserve)
- AMH modifications at 6 and 12 months follow up
- Cyst recurrence rate at 3, 6, 12 and 24 months postoperatively (visualized by transvaginal ultrasound)
- Clinical pregnancy (as defined by the ICMART (16) as a pregnancy diagnosed by ultrasonographic visualization of one or more gestational sacs or definitive clinical signs of pregnancy. It includes ectopic pregnancy. Note: Multiple gestational sacs are counted as one clinical pregnancy.)
- Ectopic pregnancy (as defined by the ICMART (16) as a pregnancy in which implantation takes place outside the uterine cavity)
- Miscarriage (defined as a spontaneous loss of pregnancy)
- Live birth (as defined by the ICMART (16) as the complete expulsion or extraction from its mother of a product of fertilization, irrespective of the duration of the pregnancy, which, after such separation, breathes or shows any other evidence of life, such as heart beat, umbilical cord pulsation, or definite movement of voluntary muscles, irrespective of whether the umbilical cord has been cut or the placenta is attached.
- Evolution of pain patterns pre- and postoperatively: each endometriosis related pain complaint will be evaluated using the NRS scale at each visit.
- POI postoperatively

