#### 7.4.5 Death

All deaths will be reported without delay to the Sponsor (irrespective of whether the death is related to the intervention or is an unrelated event). The sponsor will notify all deaths, as soon as possible after becoming aware, to the Central EC and the EC of the concerned site and provide additional information if requested.

Reporting requirements to Ethics Committee's (EC's) The Investigator is responsible for ensuring that all safety events are recorded in the (e)CRF and reported to the Sponsor.

The Sponsor will promptly evaluate all SAEs and AESIs against medical experience to identify and expeditiously communicate possible new safety findings to Investigators and based on applicable legislation.

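### Section 7.4.4 exempts pregnancy from safety reporting without exception, which conflicts with the protocol's SAE rules, so serious pregnancy complications and congenital anomalies may miss SAE reporting

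*Protocol*

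**What the plan says.** Section 7.4.4 asks women to tell the investigator at once if they become pregnant, and then instructs sites: "Pregnancy is a secondary outcome in the study, is no (S)AE and should therefore not be reported to the Sponsor". The section says nothing more about complications, pregnancy outcome or the child.

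Five other places bear on the same events.

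- **Sections 2 and 6.1.2** list clinical pregnancy, ectopic pregnancy, miscarriage and live birth as secondary outcomes. Of clinical pregnancy they say: "It includes ectopic pregnancy".
- **Section 7.2.2** defines an SAE. Its criteria include an event that "requires hospitalization or prolongation of existing inpatients' hospitalization", an event that is life-threatening, and one that "is a congenital anomaly or birth defect; or". Elective admissions do not count.
- **Section 7.3** opens with "The following events are considered reportable" and puts any SAE at the head of the list. It then gives exemptions, introduced by "For this study the following serious adverse events are not to be considered as SAE and should not be reported to the Sponsor". The five items are pre-planned admission, admission that is a standard part of the protocol treatment, admission for technical, practical or social reasons, and two on treatment of pre-existing disease that has not become worse.
- **Section 7.4.5** says "All deaths will be reported without delay to the Sponsor", and adds: "The Investigator is responsible for ensuring that all safety events are recorded in the (e)CRF and reported to the Sponsor".
- **Section 7.4.7** sets 24 hours for an SAE to reach the sponsor, subject to exceptions that the protocol defines.

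**The concern.** Section 7.4.4 reasons that pregnancy is a secondary outcome, that it is therefore not an (S)AE, and that it is therefore not reported. Treating an uncomplicated pregnancy in this way is proper. The difficulty is that the sentence has no limit, and the protocol's own definition brings a potentially serious complication, ectopic pregnancy, under the word pregnancy.

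These events are foreseeable in this trial. Infertility is one of the two qualifying complaints in section 4.2. Follow-up runs to 24 months, and section 8.4 allows a further 9 months so that pregnancies can be followed to delivery.

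What is at stake is whether a serious pregnancy complication reaches the sponsor promptly as an SAE and, for a congenital anomaly, whether the trial records it at all. Section 10.2 plans no audit or monitoring, so no planned check would show how sites read the two rules.

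**Working it through.** The protocol gives no figure to reproduce, and no arithmetic applies. The check is to take each kind of pregnancy event through the relevant sections and see whether they give the same instruction.

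| Event | Section 7.2.2 | Section 7.3 | Section 7.4.4 | Other listed route |
|---|---|---|---|---|
| Uncomplicated pregnancy, live birth | No criterion met | Not reportable | Not reported | Secondary outcome |
| Ectopic pregnancy with unplanned admission | Hospitalisation met; may be life-threatening | Reportable; no exemption fits | Not reported: ectopic pregnancy lies inside clinical pregnancy | Secondary outcome |
| Miscarriage with unplanned admission | Hospitalisation met | Reportable; no exemption fits | Not stated, but the reason given (secondary outcome) applies to it | Secondary outcome |
| Other pregnancy complication with unplanned admission | Hospitalisation met | Reportable; no exemption fits | Not stated | No endpoint of its own |
| Congenital anomaly | Named criterion | Reportable; no exemption fits | Not stated | None |
| Death | Named criterion | Reportable | Overridden by 7.4.5 | Section 7.4.5 |

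Four results follow.

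1. **Where the sections agree.** For an uncomplicated pregnancy and for a death, all sections can be followed together.

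2. **Where they contradict each other.** For an ectopic pregnancy with unplanned admission, 7.3 and 7.4.5 say report and 7.4.4 says do not. The conflict comes from the protocol's own definition of clinical pregnancy.

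3. **Where they leave the site to choose.** For miscarriage, other complications and congenital anomaly, 7.4.4 can be read either way. The table in 7.4.7 does not settle this, because it admits exceptions defined elsewhere in the protocol and a site could take 7.4.4 to be one. The reason given in 7.4.4 does not settle it either: premature ovarian insufficiency is also a secondary outcome, yet 7.3 names it as reportable. Secondary-outcome status alone therefore does not decide the question in this protocol.

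4. **What is recorded in any case.** Ectopic pregnancy and miscarriage are secondary outcomes, and section 4.5 requires follow-up of the pregnancy outcome, so the events themselves would be in the data. Congenital anomaly differs. It does not appear among the endpoints in 6.1.2, the follow-up items in 6.1.3 or the variables in 8.2, and the definition of live birth asks only for signs of life. The general recording of AEs in 7.4 is no safe substitute, since it depends on the site regarding the event as an AE, which is the point 7.4.4 puts in doubt.

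**The case against.** The strongest reply is that the sections can be read together. Section 7.4.4 speaks of pregnancy and not of its complications. Pregnancy in itself is then no SAE, while a complication that meets 7.2.2 remains one. The exemptions in 7.3 do not name pregnancy complications, and 7.4.5 obliges the investigator to report all safety events. This is a reasonable reading and probably the intended one. It is not written down, however, and for ectopic pregnancy it runs against the protocol's own definition. The reply therefore reduces the certainty of harm but does not remove the conflict.

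A second reply is that premature ovarian insufficiency is named in 7.3 because it is a plausible harm of ovarian surgery, so naming it does not imply that every secondary outcome must be reported. That is fair. The comparison shows only that being a secondary outcome is not in itself a reason against reporting.

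Some stronger inferences are tempting, and the document does not support them.

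- *Serious pregnancy events will go unreported.* Section 7.3 still applies to any SAE, so the text supports only that they may.
- *Ectopic pregnancies and miscarriages would be lost.* They remain secondary outcomes. What may be missed is the SAE form and its timeline.
- *The DSMB would not see them.* Sections 7.1 and 7.5 do not confine the DSMB to SAE forms.
- *The annual report would be incomplete.* Section 7.4.6 asks for an overview of SARs, together with new safety information. A pregnancy SAE judged unrelated to surgery would not belong in that overview anyway.
- *These events would be a large share of all SAEs.* Section 7.1 says only that unexpected severe events are not anticipated. It does not predict few SAEs, and 7.3 foresees reportable admissions for surgical complications.
- *Differences between centres would distort the comparison.* Randomisation is blocked within centre, and no comparison of SAE counts between centres is planned.

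**Conclusion.** The point holds as an internal conflict in the safety-reporting rules. Section 7.4.4, taken as written, withholds from SAE reporting an event that 7.2.2, 7.3 and 7.4.5 require to be reported, and it leaves other serious pregnancy events open to either reading. Serious complications may therefore miss SAE reporting and the 24-hour timeline. The weakest place is congenital anomaly, an explicit SAE criterion with no other listed route into the trial's data.

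The size cannot be put as a number. The protocol gives no expected pregnancy rate and no rate of complications, so any count of affected events would rest on outside assumptions. The conclusion needs only one assumption: that at least some sites apply 7.4.4 literally. The primary AMH analysis, the sample size and the randomisation are unaffected. The change is worth making because the text gives opposite instructions for a foreseeable serious event and the repair is short.

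**What to change.** Reconcile 7.4.4 with 7.2.2 and 7.3 by stating three things:

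- A pregnancy in itself is not an (S)AE and is recorded as an outcome only.
- Any pregnancy event that meets a criterion in 7.2.2, including an ectopic pregnancy or a miscarriage, is reported as an SAE under 7.3 and within the timeline in 7.4.7, in addition to being recorded as an outcome.
- Any congenital anomaly is reported in the same way.

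Record congenital anomaly (yes/no) in the eCRF together with the pregnancy outcome.

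The cost is one or two sentences in the protocol, one eCRF item and a few extra SAE forms. The change concerns reporting only and leaves the care of participants as it is.

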#### 7.4.5 Death

All deaths will be reported without delay to the Sponsor (irrespective of whether the death is related to the intervention or is an unrelated event). The sponsor will notify all deaths, as soon as possible after becoming aware, to the Central EC and the EC of the concerned site and provide additional information if requested.

Reporting requirements to Ethics Committee's (EC's) The Investigator is responsible for ensuring that all safety events are recorded in the (e)CRF and reported to the Sponsor.

The Sponsor will promptly evaluate all SAEs and AESIs against medical experience to identify and expeditiously communicate possible new safety findings to Investigators and based on applicable legislation.

#### 7.4.6 Annual reporting

The sponsor has the obligation to, once a year throughout the clinical trial (or on request), submit a progress report to the EC's containing an overview of all SARs occurred during the reporting period and taking into account all new available safety information received during the reporting period.

#### 7.4.7 Overview reporting requirements

|              | WHAT | HOW      | TO      | TIMELINES                                                                                                 |
|--------------|------|----------|---------|-----------------------------------------------------------------------------------------------------------|
| Investigator | AE   | AE form  | sponsor | as defined in protocol                                                                                    |
|              | SAE  | SAE form | sponsor | Immediately (within 24 hours of becoming aware of the event)
Exceptions: as defined in protocol |

|         | death                  | SAE form             | sponsor           | asap     |
|---------|------------------------|----------------------|-------------------|----------|
| Sponsor | death                  | SAE form + narrative | Ethics Committees | asap     |
|         | Annual Progress Report | APR template         | Ethics Committees | annually |

## 7.5 Data Safety Monitoring Board (DSMB)

Following person(s) will be part of the DSMB:

- independent statistician of the KULeuven (no conflict of interest concerning this trial).

The advice(s) of the DSMB will only be sent to the sponsor of the study. Should the sponsor decide not to fully implement the advice of the DSMB, the sponsor will send the advice to the reviewing METC, including a note to substantiate why (part of) the advice of the DSMB will not be followed.

## 8. STATISTICAL ANALYSIS

### 8.1 Sample size calculation:

Sample size calculation is based on the primary outcome: evaluation of serum AMH 3 months after the specific surgical treatment.

Power calculation of this study was based on the findings of the RCT from Candiani et al (8) where AMH was a secondary outcome in comparing conventional cystectomy versus CO2 laser vaporization. In this paper a postoperative AMH of  $1,9 \pm 0,9$  ng/mL was found after CO2 laser vaporization only. In this paper a difference in decline in postoperative AMH of 50% was observed in favor of the vaporization group, although this study was not powered for this outcome. Since we will compare two conservative techniques for endometrioma surgery, a difference of 30% AMH decline after surgery was considered to be clinically relevant (after consultation of all participating centers). Based on Candiani et al. (2018) a mean serum AMH of 1.9 (SD=0.9) ng/mL is expected with CO2 laser vaporization. Assuming a common standard deviation a total sample size of 82 patients is needed (or 41 patients in each group) based on a two-sided independent t-test with alpha equal to 0.05 to have at least 80% power to detect a difference of 30% between both groups. Note that this calculation is based on the conservative assumption of no correlation between baseline AMH and AMH after 3 months.

In practice, the power is expected to exceed largely 80% since the final analysis will be based on an ANCOVA approach. However, since the study wants to gather information on multiple endpoints, we deemed it not appropriate to lower the sample size.

To account for the 10% drop out because of pregnancy within 3 months postoperatively, it is prudent to aim for a total sample size of 92 patients (or 46 patients in each group).

